#### Sample size calculation

The sample size was based on detecting a difference of 3 mm Hg (SD=12 mm Hg) in systolic blood pressure between each of the experimental drugs and the placebo treatment with 90% power, and using a single sample t test at the 0.003 significance level (0.01 level adjusted for 3 comparisons being made). Variances in these calculations were estimated from the within-subject (interdrug) variability observed in 90 patients participating in the Cambridge crossover studies of the major drug classes.

The estimated requirement was for 294 patients; so we set a recruitment target of 346 to allowing for a dropout rate of 15%. This number also provides similar power to detect a twofold increase in superiority through renin profiling, namely a 6 mm Hg difference in systolic BP between best and second-best drug within each quartile of plasma renin.

#### Statistical model

The protocol requires patients to take triplicate morning and evening HBPM BP readings for the 4 days before each study visit, a total of 24 readings per visit. We shall use the arithmetic mean of last 18 measurements prior to a study visit to calculate home blood pressure. If more than 18 measurements have been obtained, the earliest recorded readings will be discarded. Thus, for most patients we will use all the readings on days 1 to 3 prior to the visit, but if any of these are missing then readings from day 4 will be used instead. The minimum number of measurements required for a valid assessment of home blood pressure using home BPM is six. Means of the morning and evening readings will be used in all subsequent analysis.

We shall use a mixed model to analyse HBPM BP, with unstructured covariances for the repeated measures for a patient. The model will include terms for time of day (morning or evening), gender, age, height, weight and smoking history. We will also adjust for baseline BP. If any of the baseline BPs cannot be estimated, we will substitute the overall mean baseline value, set an indicator variable to denote an imputed value and include the indicator variable in the model. The model will also include terms for treatment and phase (to allow for period effects), and an indicator variable to identify the subgroup of patients whose crossover treatments were unblinded.

*The primary analysis* will use BPs recorded for the maximum tolerated dose of each drug. The first of the primary end points is the mean difference between spironolactone and placebo; the second is the mean difference between spironolactone and the average of other active treatments; and the third and fourth are the mean differences between spironolactone and each of the other active treatments taken individually.

*The secondary analysis* will estimate for each treatment: changes in home BP; clinic BP on maximum tolerated dose, and changes in clinic BP; responder rates; withdrawals due to adverse events; and haemodynamic variables and pulse wave analyses. We shall use mixed models to analyse the continuous variables and these will include baseline covariates.

A patient will be deemed a “responder’ if they meet any of these two conditions; (1) HBPM systolic BP (SBP) <135 mm Hg; (2) HBPM SBP has fallen ≥10 mm Hg since baseline. Responder rates will be analysed by logistic regression and will be adjusted for baseline covariates. Withdrawal rates will be analysed by logistic regression and will be adjusted for baseline covariates.

The main secondary objective is to use plasma renin measurements to evaluate an ‘α, β, Δ’ rule for the selection of the fourth-line drug for patients with drug-resistant hypertension (see secondary objectives above). The hypothesis is that plasma renin (measured on a background of 3 drugs, ie, A+C+D), will predict the most effective fourth-line drug. We shall identify the best treatment for each patient, that is, the one on which they achieved the lowest BP. This is a categorical response and we shall use a logistic model to estimate the probability of each treatment being declared the best as a function of baseline renin. Superimposed plots of these probabilities (see figure 2) will show the range of renin values for which each treatment is most likely to be the best choice. We will also, in the same way, evaluate haemodynamic parameters indicative of sodium retention and volume status, that is, cardiac output, peripheral resistance and bioimpedance as predictors of the best fourth-line treatment among the three active treatments. An additional end point will be analyses of relationships between genetic factors and pharmacodynamic responses.

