**Methods and analysis:**

Placebo-controlled, random crossover study of fourth-line treatment when added to standard (A+C+D) triple drug therapy: ACE inhibitor or Angiotensin receptor blocker (A) +Calcium channel blocker (C)+Diuretic (D). Patients (aged 18–79 years) with clinical systolic BP≥140 mm Hg (135 mm Hg in diabetics) and Home BP Monitoring (HBPM) systolic BP average ≥130 mm Hg on treatment for at least 3 months with maximum tolerated doses of A+C+D are randomised to four consecutive randomly allocated 12-week treatment cycles with an α-blocker, β-blocker, spironolactone and placebo. The hierarchical coprimary end point is the difference in HBPM average systolic BP between (in order) spironolactone and placebo, spironolactone and the average of the other two active drugs, spironolactone and each of the other two drugs. A key secondary outcome is to determine whether plasma renin predicts the BP response to the different drugs. A sample size of 346 (allowing 15% dropouts) will confer 90% power to detect a 3 mm Hg HBPM average systolic BP difference between any two drugs. The study can also detect a 6 mm Hg difference in HBPM average systolic BP between each patient's best and second-best drug predicted by tertile of plasma renin.

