Haemodynamic measures (cardiac output, peripheral resistance, bioimpedance), pulse wave analysis/velocity¶		X		X		X		X		X
Compliance check		X	X	X	X	X	X	X	X	X
Directly observed therapy		X								
AE reporting			X	X	X	X	X	X	X	X
Randomisation		X								
Dispensing	X	X	X	X	X	X	X	X	X	X

*Home BP measurements are recorded twice daily in triplicate in the 4 days leading up to the baseline visit and week 6 and week 12 visits of each treatment cycle.

†To exclude white coat hypertension and confirm adherence.

‡In the event that plasma renin/aldosterone is not taken at baseline, it will be measured at week 12 of each treatment cycle.

§Pharmacogenetics sample to be taken where specific informed consent has been given. Sampling will typically be at baseline (day 0) but may be at any time later in the study.

¶Where equipment is available.

AE, adverse events; BP, blood pressure; HCG, human chorionic gonadotropin; HDL, high-density lipoprotein; PEFR, peak expiratory flow rate.

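### The α, β, Δ renin objective is tested on a lowest-BP label, which has clearly less power than a treatment-by-renin interaction for advantages of 2 to 3 mm Hg

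*Protocol article*

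**What the plan says.** Under Secondary objectives, the main secondary aim is the α, β, Δ rule: spironolactone best in the lowest renin tertile, the α-blocker in the middle and the β-blocker in the highest. The Statistical model section gives the analysis: "We shall identify the best treatment for each patient, that is, the one on which they achieved the lowest BP". A logistic model then estimates the probability that each treatment is best as a function of baseline renin, and the fitted probabilities are plotted together.

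The same section analyses home BP as a continuous outcome in a mixed model with treatment and phase terms, baseline BP and other covariates. Renin does not appear in that model.

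The Sample size calculation section justifies this objective on a BP scale, "namely a 6 mm Hg difference in systolic BP between best and second-best drug within each quartile of plasma renin". The abstract has a looser version by tertile: "best and second-best drug predicted by tertile of plasma renin".

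The opening Statistical analysis plan section also plans to look at the direction of the correlation between renin and the response to each drug, and to describe responses at the extremes of renin. A footnote to Table 1 adds: "In the event that plasma renin/aldosterone is not taken at baseline, it will be measured at week 12 of each treatment cycle".

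**The concern.** Taking the lowest of three values turns three measurements into one category. A drug that wins by 1 mm Hg counts the same as one that wins by 15 mm Hg. Each drug is given in one period per patient, so no replicate shows whether a win would recur. The label is formed from each patient's own values, so phase effects that the mixed model would remove stay in it as extra noise.

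The objective asks whether the ranking of the drugs changes with renin. On the BP scale that is a treatment-by-renin interaction, which the crossover estimates within patients. If the formal analysis uses only the label, a renin effect of modest but useful size could be missed, and the trial could be read as evidence against renin-guided choice. The stated power gives no warning of this, because it was worked out for a different analysis.

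**Working it through.** **Inputs from the protocol article.**
- "The sample size was based on detecting a difference of 3 mm Hg (SD=12 mm Hg) in systolic blood pressure", with 90% power and alpha 0.003 (Sample size calculation).
- "Variances in these calculations were estimated from the within-subject (interdrug) variability observed in 90 patients" (same section).
- 294 evaluable patients; 346 recruited, allowing 15% dropout (same section).
- Each home BP is a mean of up to 18 readings (Statistical model); one 12-week period per drug (Study design).

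**1. Reproduce the plan's own figures.** A two-sided one-sample t test on paired differences (noncentral t, difference 3, SD 12, alpha 0.003, power 0.90) gives n = 294. Then 294/0.85 = 345.9, so 346. Both match. The 12 mm Hg is therefore the SD of a between-drug difference, and the per-period SD is 12/√2 = 8.5 mm Hg if all of it is noise.

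**2. Reproduce the renin power.** The same test with a 6 mm Hg difference gives 88% per quartile (294/4 = 73.5 patients) and 97% per tertile (294/3 = 98). The claim of similar power is sound for a mean difference within a stratum. It is not a calculation for the logistic label model.

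**3. Compare the two analyses.** Simulated trials of 294 patients, three active drugs, paired-difference SD 12 and no phase effect. The rule's drug is d mm Hg better in its own tertile. Label analysis: likelihood-ratio test of a multinomial logistic model of the lowest-BP label on renin tertile. Interaction: Wilks test of the within-patient drug contrasts across tertiles. Both have (3 − 1) × (3 − 1) = 4 degrees of freedom. In the check with no renin effect (linear log-renin coding), both rejected in about 5% of trials at alpha 0.05.

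| d (mm Hg) | Label picks the rule's drug | Label, α 0.05 | Interaction, α 0.05 | Label, α 0.003 | Interaction, α 0.003 |
|---|---|---|---|---|---|
| 2 | – | 46–48% | 74–77% | about 14% | 36–39% |
| 3 | 44% | 82–85% | 97–98% | about 54% | about 88% |
| 4 | 47% | 99% | 100% | about 90% | 100% |
| 6 | 55% | 100% | 100% | 100% | 100% |

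Ranges show the spread between independent simulation runs. Chance labelling is 33%. The article does not state an alpha for this objective, so both 0.05 and 0.003 are shown.

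**4. Same comparison with linear slopes.** Let one drug's effect weaken and another's strengthen by 1 mm Hg per SD of log renin. Power at alpha 0.05 is 40–45% for the label and 67–73% for the interaction. At 1.5 mm Hg per SD it is about 80% and 98%.

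**5. Cost in patients.** At d = 2.5 mm Hg the interaction with 294 patients has about 92% power at alpha 0.05. The label analysis reaches 92% at 500 patients. At alpha 0.003 it needs between 500 and 550. The loss of information is 1 − 294/500 = 41% to 1 − 294/550 = 47%.

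**6. Sensitivity to the SD.** If 12 mm Hg were the per-period SD, d = 3 would give 55% against 80% and d = 6 would give 99.6% against 100% (alpha 0.05). If half of the 12 mm Hg variance were real patient-by-drug variation, power at d = 3 would hardly change (84% against 99%).

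**The case against.** The best defence is that the label model answers the question as a clinician would ask it: at this renin level, which drug is most likely to be best? It also has about 100% power at 6 mm Hg, the effect that the article plans for on this objective. That stands. A reader might infer that the planned analysis would hide the planned renin effect; the figures do not support that.

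Other stronger readings also fail:
- **One BP reading per drug.** Each value averages up to 18 home readings; only the treatment period is single.
- **A mostly noise label.** The article describes the 12 mm Hg as interdrug variability and does not split it. If 25%, 50% or 75% of the variance is real patient-by-drug variation, the label finds the patient's own best drug in 53%, 65% or 76% of patients.
- **A best-versus-second-best gap inflated by chance.** With pure noise the per-patient gap averages 7.2 mm Hg, above the 6 mm Hg in the abstract. But the Statistical model section analyses the probability of being best and never a per-patient gap.
- **No continuous renin analysis.** The Statistical analysis plan section does plan correlations and a description at the extremes. As worded, they are descriptive and do not test whether the drugs differ in renin slope.
- **Renin measured on study drug spoils the test.** The model specifies baseline renin on A+C+D. The footnote has later samples taken, placebo cycle included, but nothing says that an on-drug value enters the model.
- **Bias from period effects or ties.** The 24 sequences are equally likely and baseline renin precedes treatment, so phase adds noise to the label but does not confound it with renin. Exact ties between such means should be rare.

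**Conclusion.** The point holds as one of efficiency and of mismatch between power and analysis. It is not an error that invalidates the objective. The label analysis discards roughly 40–45% of the information. At a 2 mm Hg advantage it has about 46–48% power where the interaction has 74–77%. At 3 mm Hg, the size the trial uses for its primary comparison, it has 82–85% against 97–98%. At 4 mm Hg and above the loss is negligible at alpha 0.05.

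The figures assume 294 patients, equal noise for all drugs, no phase effect, a 12 mm Hg paired-difference SD that is all noise, and three active drugs in the label. The article says each treatment, so whether placebo counts is unclear. The stated renin power cannot be carried over to the label model. The article should also settle whether strata are tertiles, as in the abstract and Secondary objectives, or quartiles, as in the Sample size calculation.

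**What to change.** Add renin and the treatment-by-log-baseline-renin interaction to the home BP mixed model, for the active drugs, and make that interaction the formal renin test. A linear log-renin term alone does not target the prediction that the α-blocker is best in the middle tertile, so include a pre-specified non-linear term or a tertile factor.

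A significant interaction does not by itself prove the rule. From the same model, report the predicted BP differences between drugs across renin, and the ranges in which each drug has the lowest predicted BP, with confidence bands. Keep the best-drug probability plot as description. State the power for the interaction. If a renin sample from a treatment cycle ever replaces a missing baseline value, use only the placebo-cycle sample.

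The cost is analysis wording and a little more modelling work, with no new data or visits. The downside is that the best drug becomes a model-based quantity and is no longer directly observed.

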**Figure 2 BMJOPEN2015008951F2:**
[figure not shown]
Predicted probabilities model for plasma renin as the predictor of the best treatment option for resistant hypertension.

#### Blinded versus unblinded cohorts

We will assess the advantage and disadvantages of using the double-blind, placebo-controlled random crossover design in comparison to the open label random crossover design. We will expand the models used to analyse the primary and secondary outcomes to estimate a cohort effect (unblinded vs blinded) within each treatment.

Patients who withdraw from the study before final visit will be included in the primary analysis if they have at least one postrandomisation HBPM, and missing data imputed by application of the last observation carried forward. Patients with data missing from any time point required for analysis, and patients in whom major violation of the protocol is documented by investigators or detected by the data management centre will be excluded from per-protocol analysis.

There will be no interim analysis, no stopping rules and no data monitoring committee. This is because all treatments are being used for licensed indications, and have been so used for several decades. We do not, therefore, anticipate any unexpected hazard that has eluded detection during many millions of person-years exposure, and the study is not powered to detect any significant differences in serious morbidity or mortality between treatment groups.

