## Methods

### Study design

PATHWAY 2 is a randomised, double blind, placebo-controlled, crossover, multicentre trial comparing the four treatment options for patients with resistant hypertension. The four treatment options are taken once daily, in addition to the maximum/best tolerated doses of three drugs at baseline according to the current NICE hypertension treatment guideline, that is, A+C+D where: A=ACE-inhibitor or Angiotensin receptor blocker; C=Calcium channel blocker; D=thiazide/thiazide-type Diuretic.^4^
^5^

After a screening visit, patients potentially eligible for randomisation proceeded to a 4-week run-in period on the patient's baseline therapy with three drugs, that is, A+C+D. After the run-in period and if still meeting the eligibility criteria, the patients were allocated double blind to a cycle of 4×once daily oral treatments in a random sequence. The randomisation is not stratified and in this 4 × 12-week period, four treatments crossover study, participants are randomised with equal probability to one of the 24 possible sequences of treatments. The treatments comprise: (1) further diuretic therapy—spironolactone; 25–50 mg, (2) α-blocker—doxazosin modified release; 4–8 mg, (3) β-blocker—bisoprolol; 5–10 mg and (4) placebo. The treatment cycles were initiated with each treatment for 6 weeks at the lower dose, followed by forced titration to twice this dose for a further 6 weeks—each cycle for a total of 12 weeks. There is no washout period between the four treatment cycles (3 active, 1 placebo), as 12 weeks of treatment per drug cycle is considered sufficient to eliminate the order effects of treatment. The total length of the trial is 52 weeks (4 weeks run-in and 4×12 week treatment cycles; figure 1).

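### Last observation carried forward in the primary analysis is not confined to a drug's own cycle, so as written one drug's BP is entered for drugs the patient never took

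*Protocol article*

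**What the plan says.** The missing-data rule stands under Blinded versus unblinded cohorts. Patients who leave before the final visit (week 48 in Table 1) remain in the primary analysis "if they have at least one postrandomisation HBPM, and missing data imputed by application of the last observation carried forward". No limit is placed on how far a value may be carried, or on which treatment it may be carried into.

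Three other parts of the article bear on this:

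- **Study design.** There are four 12-week cycles, each with a different treatment; "participants are randomised with equal probability to one of the 24 possible sequences of treatments". "There is no washout period between the four treatment cycles".
- **Home blood pressure monitoring and Table 1.** Home readings are due at weeks 6 and 12 of each cycle.
- **Statistical model.** "We shall use a mixed model to analyse HBPM BP, with unstructured covariances for the repeated measures for a patient", with terms for treatment and phase. The primary analysis is to take the pressures measured on each drug at the highest dose the patient tolerated. "The first of the primary end points is the mean difference between spironolactone and placebo"; the others compare spironolactone with the average of doxazosin and bisoprolol, and then with each of them.

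**The concern.** In a parallel-group trial, carrying the last value forward at least stays within the assigned treatment. In this crossover it does not. A patient who leaves after the bisoprolol cycle with spironolactone and placebo still to come would have the bisoprolol pressure entered three times, once under its own name and twice under the names of treatments not taken. The within-patient differences between those three are then zero by construction.

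The primary end points are these differences between drugs, so the filled values act directly on the estimates. A carried value is also not a pressure measured on the drug to which it is assigned, so the missing-data paragraph and the Statistical model section do not agree. The filling is unnecessary as well: a mixed model with treatment and phase terms can use the observed cycles of an incomplete patient without imputation, validly if data are missing at random. At stake are the size of the reported treatment effects and the width of their intervals, in a trial that expects to inform guidelines.

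**Working it through.** **1. Inputs.** From Sample size calculation: a 3 mm Hg difference of an active drug from placebo, SD 12 mm Hg, power 90%, by a single-sample t test at the 0.003 level. The same section gives the numbers: "The estimated requirement was for 294 patients; so we set a recruitment target of 346 to allowing for a dropout rate of 15" per cent. From Study design: four treatments, 24 equally likely sequences. The article does not give the timing of withdrawal or its relation to drug. These are assumptions here, and ranges are shown.

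**2. The plan's own figure.** Normal approximation, two-sided: n = (2.968 + 1.282)² × (12/3)² = 18.06 × 16 = 289. The exact noncentral-t calculation gives n = 294, with power 90.1%. For dropout, 294/0.85 = 346. Both stated figures reproduce.

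**3. What a filled patient contributes.** Suppose a patient leaves after completing cycle k, for reasons unrelated to drug. Write m(A) for the true mean on drug A and T for the sum of the four means.

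- With probability k/4, drug A was taken and its own value is used.
- With probability (4 − k)/4 it was not. The filled value then comes from the last drug taken, which is equally likely to be any of the other three, with mean (T − m(A))/3.

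The expected entry for A is (k/4)·m(A) + ((4 − k)/12)·(T − m(A)). Subtracting the same expression for drug B gives

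(m(A) − m(B)) × [k/4 − (4 − k)/12] = (m(A) − m(B)) × (k − 1)/3.

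Such a patient therefore contributes 0, 1/3 or 2/3 of the true difference for k = 1, 2 or 3. The expression is linear in the means, so the same fractions apply to spironolactone against the average of the other two actives. Enumerating all 24 sequences gave the same fractions.

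**4. Effect on the whole trial.** With a proportion d of patients filled, the retained fraction is 1 − d × (1 − (k − 1)/3). For d = 0.15:

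| Timing of withdrawal (assumed) | Retained | True 3.0 mm Hg becomes |
|---|---|---|
| all after cycle 1 | 0.85 | 2.55 |
| evenly after cycles 1, 2, 3 | 1 − 0.15 × 2/3 = 0.90 | 2.70 |
| all after cycle 3 | 0.95 | 2.85 |

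The rule fills only patients with at least one post-randomisation home BP. If a third of the dropouts left before any reading (assumed), 10% of those randomised would be filled among the 95% analysed. The retained fraction with even timing is then (0.85 + 0.10/3)/0.95 = 0.93, or 2.79 mm Hg.

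**5. Coverage and power.** Simulation with 346 patients, SD of the paired difference 12, 15% withdrawal unrelated to drug, a true difference of 3 mm Hg, 4,000 runs per scenario and a simple paired analysis:

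| Timing | Mean, carried forward | Mean, observed pairs | Coverage, carried forward | Coverage, observed pairs | Power at 0.003, carried forward / observed |
|---|---|---|---|---|---|
| even | 2.71 | 3.01 | 92% | 94% | 91% / 91% |
| all after cycle 1 | 2.53 | 2.98 | 88% | 95% | 90% / 90% |
| all after cycle 3 | 2.85 | 3.00 | 94% | 94% | 92% / 93% |

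Power hardly moves because the artificial zeros also reduce the variance and the number analysed stays at 346. The stated unstructured-covariance model was not fitted, so coverage and power are illustrative.

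**6. Withdrawal that depends on drug.** Assume means of 0, −3, −6 and −8 for placebo, doxazosin, bisoprolol and spironolactone, and patients who stop on starting bisoprolol in cycle 2, 3 or 4 (equally likely) before any reading on it. Bisoprolol is filled with the mean of the other three: (0 − 3 − 8)/3 = −3.67. Spironolactone was taken by 2/3 of these patients on average; otherwise it is filled from placebo or doxazosin, mean −1.5. Its expected entry is (2/3)(−8) + (1/3)(−1.5) = −5.83. The difference is −5.83 + 3.67 = −2.17 against a true −2, or 1.08 times the truth among those who withdrew. Spironolactone minus placebo shrank in every scenario run.

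**The case against.** **The rule may mean week 6 to week 12 within the same drug.** That reading would agree with the Statistical model section and would not have this fault, and an analysis plan not shown here may say so. However, the sentence concerns withdrawal from the study, sets no such limit, and admits a patient with a single home reading, most of whose missing data belong to other treatments. An analyst who followed it literally would fill across drugs. If the narrower rule was meant, the wording still needs correcting.

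**The error is conservative and decisions are little affected.** Much of this stands. With withdrawal unrelated to drug, power is about the same either way, and a paired simulation under no difference gave rejection rates with carry-forward of 4.8% at the 0.05 level and 0.28% at 0.003, so no inflation. A reader might infer that the trial loses power or gains false positives; the figures support neither. The estimate and its coverage still suffer.

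**Fewer patients may be filled than 15%.** This also stands. Some dropouts will have no reading at all, and Special considerations lets a patient who cannot tolerate one drug move to the next, so intolerance need not mean withdrawal. Both reduce the effect without removing it.

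**A per-protocol analysis excludes patients with missing data.** It gives a comparison free of carried values, but it is not the primary analysis and it discards observed cycles.

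**Two wider readings do not hold.** A reader might infer that every primary difference must shrink. That holds in expectation when withdrawal is unrelated to drug, but step 6 shows that a contrast between active drugs can be overstated otherwise. A reader might also infer that filled values create ties when each patient's best drug is identified. The article states carry-forward for the primary analysis only, and defines the best drug by the lowest pressure achieved on it; nothing extends the rule to that analysis.

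**Conclusion.** The concern holds for the rule as written: carry-forward without a cycle limit does not suit a crossover and contradicts the article's own definition of the primary analysis data. If withdrawal is unrelated to drug and all 15% planned dropouts are filled, the primary contrasts shrink in expectation by 5% to 15%, about 10% with even timing (0.3 mm Hg on 3.0), and by less if some leave before any home reading. Coverage of the nominal 95% interval is then about 92% (88% to 94%) under a simple paired analysis. The harm is bias and under-coverage, with power about unchanged. If withdrawal depends on the drug, the direction of bias in a comparison between active drugs is not assured. Timing and cause of withdrawal are assumptions throughout; the article gives only the 15% rate.

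**What to change.** Remove carry-forward across treatment cycles from the primary analysis. State that the mixed model is fitted to the observed cycles of all patients with at least one post-randomisation home BP, under a missing-at-random assumption. If any carry-forward is kept, say that it stays within the same drug's cycle, from week 6 to week 12. A sensitivity analysis for informative withdrawal would be a reasonable optional addition.

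The cost is one sentence of wording before the data are analysed, and a slightly wider interval. In an illustrative within-patient fixed-effects simulation (true difference 6.0 mm Hg) the standard error was 0.68 with observed cycles and 0.62 with carried values, a ratio of 0.68/0.62 = 1.10. The narrower interval was centred on a shrunken estimate of 5.4.
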